#### **10.5.5.2 Laboratory abnormalities**

All laboratory values will be converted into SI units and the severity grade calculated using appropriate common terminology criteria for adverse events (CTCAE, version 3.0) unless otherwise indicated.

Renal function will be assessed using the calculated creatinine clearance (CrCl) from the Cockcroft-Gault formula ([Cockcroft et al 1976](#)). The proportions of patients in each treatment group with severe renal impairment (defined as calculated CrCl < 30 mL/min) will be compared numerically. In addition, the proportion of patients with NCI CTCAE grade 3/4 serum creatinine will be determined for each treatment group and compared.

A listing of laboratory values will be provided by laboratory parameter and by patient. The frequency of notable lab abnormalities will be displayed by parameter.

Similarly, the frequency of all laboratory abnormalities will be displayed by parameter and worst CTCAE grade experienced.

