| Safety assessments                      | 
Toxicity will be assessed by the NCI CTCAE v3.0 (http://ctep.cancer.gov/forms/CTCAEv3.pdf). The NCI CTCAE has been chosen in order to be consistent with other RAD001 trials. Safety assessments will include monitoring and recording of all AEs and SAEs at every visit, and monitoring of vital signs, physical condition and body weight. Laboratory assessments including hematology and blood chemistry (including serum creatinine and calculated creatinine clearance) will be done every two weeks for the first 8 weeks, at 12, 18 and 24 weeks and every 12 weeks thereafter.
 
Patient should report any angiomyolipoma-related bleeding events to the site.
                                                                                                                                                                                                                                                                                                                                                                                                                                                                                                                                                                                                                                                                                                                                                                                                                                                                                                                                                                                                                                                                                                                                                                                                                                                                                                               |

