| Triglycerides increased                                                                                        | 73                          | <1           | 0            | 34               | 0            | 0            |
| Glucose increased                                                                                              | 57                          | 15           | <1           | 25               | 1.5          | 0            |
| Creatinine increased                                                                                           | 50                          | 1.5          | 0            | 34               | 0            | 0            |
| Phosphate decreased                                                                                            | 37                          | 6.2          | 0            | 8.0              | 0            | 0            |
| Aspartate transaminase (AST) increased                                                                         | 25                          | <1           | <1           | 6.6              | 0            | 0            |
| Alanine transaminase (ALT) increased                                                                           | 21                          | 1.1          | 0            | 3.6              | 0            | 0            |
| Bilirubin increased                                                                                            | 2.9                         | <1           | <1           | 2.2              | 0            | 0            |
| CTCAE Version 3.0                                                                                              |                             |              |              |                  |              |              |
| a Includes reports of anaemia, leucopenia, lymphopenia, neutropenia, pancytopenia, thrombocytopenia |                             |              |              |                  |              |              |

For further information about side effects and their management, see [Section 6.1.1](#) and [Section 6.1.2](#).

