### 3.2 Secondary objectives

To compare RAD001 versus placebo with respect to:

1. Time to angiomyolipoma progression.

2. Skin lesion response rate.
3. Change from baseline in plasma angiogenic molecules, e.g., VEGF, basic FGF, PLGF, soluble VEGF receptor1, and soluble VEGF receptor2.
4. Renal function assessed using calculated creatinine clearance
5. Safety as assessed by the National Cancer Institute's (NCI) Common Terminology Criteria for Adverse Events (CTCAE), version 3.0.

In RAD001 treatment arm to:

1. Characterize the pharmacokinetics of RAD001 in this patient population, specifically in terms of exposure.
2. Describe the time to angiomyolipoma response, the duration of angiomyolipoma response, and the duration of skin lesion response.

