- Note: patients with vagal nerve stimulators are permitted to have CT assessments of angiomyolipoma unless local or national regulations do not permit this.
19. Serum creatinine  $> 1.5 \times$  ULN.
  20. History of malignancy in the past two years, other than squamous or basal cell skin cancer.
  21. Any severe and/or uncontrolled medical conditions which could cause unacceptable safety risks or compromise compliance with the protocol, such as:
    - $\geq$  Grade 3 hypercholesterolemia/hypertriglyceridemia or  $\geq$  Grade 2 hypercholesterolemia/hypertriglyceridemia with history of coronary artery disease (despite lipid-lowering treatment if given)
    - Impairment of gastrointestinal function or gastrointestinal disease that may significantly alter the absorption of study drug (e.g., ulcerative disease, uncontrolled nausea, vomiting, diarrhea, malabsorption syndrome).
    - Active skin, mucosa, ocular or GI disorders of Grade  $> 1$

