### **10.5.5 Safety**

The assessment of safety will be based mainly on the frequency of adverse events (AEs) and on the number of laboratory values that fall outside of pre-determined ranges. Other safety data (e.g., electrocardiogram, vital signs) will be considered as appropriate. All safety data will be listed.

For all safety analyses, the safety population will be used.

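### The only stated analysis of creatinine clearance is a count below 30 mL/min with no baseline reference, which is very unlikely to answer the between-arm renal objective

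*Protocol*

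**What the plan says.** Section 3.2, under the comparisons of RAD001 with placebo, lists as item 4 "Renal function assessed using calculated creatinine clearance". The synopsis repeats it, and in its endpoint list places creatinine clearance under safety.

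Section 10.5.5.2 fixes the analysis in three parts:

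- For CrCl: "The proportions of patients in each treatment group with severe renal impairment (defined as calculated CrCl < 30 mL/min) will be compared numerically".
- For serum creatinine: "the proportion of patients with NCI CTCAE grade 3/4 serum creatinine will be determined for each treatment group and compared".
- For laboratory data in general: "the frequency of all laboratory abnormalities will be displayed by parameter and worst CTCAE grade experienced". Individual values are also listed.

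Section 10.5.5 adds: "For all safety analyses, the safety population will be used".

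The data are frequent. The synopsis says blood chemistry, "including serum creatinine and calculated creatinine clearance) will be done every two weeks for the first 8 weeks", then at weeks 12, 18 and 24 and every 12 weeks. The renal entry restriction in Section 5.2 is "Serum creatinine $> 1.5 \times$ ULN"; there is no CrCl criterion. For comparison, Section 10.5.10 plans summaries of raw values and changes from baseline, plus longitudinal models, for the angiogenesis markers, which are item 3 of the same list.

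**The concern.** A continuous measure taken at nearly every visit is reduced to one extreme category, and the category is not tied to the patient's own starting value. A fall from 90 to 60 mL/min, a rise from 60 to 75 and no change at all give the same entry: not below 30. A patient already below 30 at entry may be counted as severely impaired without any change.

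Section 1.2 names encroachment on renal tissue, possibly leading to renal failure, as one of the two morbidities of renal angiomyolipoma, and treats preservation of renal function as key to long-term outcome. Preservation is something a count of severe impairment in a trial of this size can hardly show. A near-empty table could be read as evidence of no renal difference when it is evidence of very little.

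**Working it through.** **Plan's own figure.** The protocol states no precision or power for the renal comparison. The exact method used below, applied to the primary comparison in Section 10.7 (66 versus 33, 20% versus 0%, one-sided 2.5%), gives 93.2%, against the stated 93% for Fisher's test.

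**1. What each display can show.**

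| Display in 10.5.5.2 | Any-grade creatinine rise | Size of CrCl difference | Preserved or improved CrCl | Tied to baseline |
|---|---|---|---|---|
| CrCl < 30 mL/min | no | no | no | no |
| Grade 3/4 creatinine | no | no | no | not stated |
| Worst CTCAE grade | yes | no | no | not stated |

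**2. Information in the threshold count.** If all k events fall on RAD001, the one-sided exact p-value is C(66,k)/C(99,k). For k = 8 this is 0.034; for k = 9 it is 0.021. So 9 versus 0 is needed, and 9/66 = 13.6%. With no events at all, the upper 95% limit is 1 − 0.025^(1/n): 5.4% for 0/66 and 10.6% for 0/33.

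No test is planned, so the following gauges information only. Exact power is the sum, over all outcomes (x, y) with Fisher p at or below the level, of Bin(x; 66, p1) × Bin(y; 33, p2). All rates are assumed except the first row.

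| RAD001 vs placebo | One-sided 2.5%, in the direction of the difference | Two-sided 5% |
|---|---|---|
| 1.5% vs 0% | about 0 | about 0 |
| 5% vs 1% | 0.4% | 1.2% |
| 10% vs 3% | 8% | 13% |
| 10% vs 0% | 21% | 34% |
| 0% vs 5% | 8% | 23% |
| 1% vs 10% | 31% | 51% |

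The first row uses the grade 3 rates for "Creatinine increased" in Table 1-4 (grade 4 was 0% in both arms). It implies 66 × 0.015 = 0.99 expected events and a chance of none of 0.985^66 = 37%. Those rates come from metastatic renal cell carcinoma and concern creatinine, not CrCl, so they only illustrate.

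**3. Entry CrCl.** Section 7.6.5.4 gives CrCl = (140 − age) × weight × constant / creatinine, with constant 1.04 for women. Assume an upper limit of normal (ULN) of 90 µmol/L, so the entry ceiling is 1.5 × 90 = 135.

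- Woman aged 40, 65 kg: 100 × 65 × 1.04 / 135 = 50 mL/min. To reach 30 her creatinine must be 6760/30 = 225 µmol/L, or 2.5 × ULN.
- Woman aged 55, 45 kg: 85 × 45 × 1.04 / 135 = 29.5 mL/min. She is eligible on creatinine and already below 30.

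The same cut-off is therefore remote for one eligible patient and already crossed by another.

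**4. A change-from-baseline estimate instead.** Half-width = 1.96 × SD × √(1/66 + 1/33) = 0.418 × SD. The SD of change is not in the protocol. Assumed SDs of 10, 15, 20 and 25 mL/min give 4.2, 6.3, 8.4 and 10.4 mL/min, before any gain from baseline adjustment.

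**The case against.** The strongest reply is that this is safety monitoring. The synopsis places CrCl under safety endpoints, Section 10.5 confines the secondary efficacy objectives to progression and skin response, and renal function is outside the closed testing procedure of Section 10.5.3. No test is planned, so low power is no fault in itself. Change-from-baseline laboratory summaries are often left to the SAP, which was not available here. All of this stands, and it limits the weight of the point. It does not remove it. The protocol states a method for this objective, and that method does not estimate the quantity the objective names; Section 10.5.10 shows that change from baseline was specified where it was wanted.

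A reader might infer three stronger things, which the document does not support:

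- *Renal function is examined only through extreme events, so harm would be missed.* The worst-grade table would show any-grade creatinine rises such as the 50% versus 34% in Table 1-4. It is not a sharp instrument at this size (exact power at those rates is about 25% one-sided 2.5%), but it is not blind.
- *Severe impairment is known to be rare here, because high creatinine is excluded.* No rate of CrCl below 30 in this population is given, and the creatinine limit does not bar CrCl below 30 at entry.
- *The objective cannot be answered.* The data are collected, so it can be; the stated analysis is what falls short.

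**Conclusion.** The point holds as a mismatch between a declared comparison and its stated analysis. Section 3.2 asks for a between-arm comparison of CrCl. Section 10.5.5.2 gives a count below 30 mL/min with no baseline reference, plus two displays of creatinine grade. None yields a CrCl difference or could show preserved or moderately changed clearance, so the stated analysis is very unlikely to answer the objective with 66 versus 33 patients.

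The 9-versus-0 requirement and the zero-event limits follow from the sample size alone. The power figures rest on assumed rates, or in one row on rates borrowed from another disease and another measure. The half-widths rest on assumed SDs, and the entry examples on an assumed ULN and chosen ages and weights. The primary endpoint, type I error and sample size are unaffected. The change is worth making because a declared objective otherwise lacks a suitable stated analysis and the remedy is nearly free.

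**What to change.** In Section 10.5.5.2:

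- Add the between-arm difference in change from baseline in Cockcroft-Gault CrCl during blinded treatment, with a 95% confidence interval. It could be adjusted for baseline CrCl and the stratification factor. A repeated-measures model or an analysis of covariance at week 24 would both serve; the essential item is the estimate and its interval.
- State that this is a descriptive estimate outside the hierarchy of Section 10.5.3.
- Keep the counts of CrCl below 30 mL/min and of grade 3/4 creatinine as safety displays, but report them as shifts from baseline so that patients already past the threshold at entry are visible.

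The cost is one extra analysis of creatinine and weight already collected. No visit, sample, patient or alpha is added.

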#### **10.5.5.3 Other safety data**

Safety data from other tests (e.g., electrocardiogram or vital signs) will be listed, notable values flagged, and any other information collected will be listed as appropriate. Any

statistical tests performed to explore the data will be used only to highlight any interesting comparisons that may warrant further consideration.

#### **10.5.6 Tolerability**

Not applicable for this study.

#### **10.5.7 Resource utilization**

Not applicable for this study.

#### **10.5.8 Patient-reported outcomes**

Not applicable for this study.

#### **10.5.9 Pharmacokinetics**

Pre-dose trough concentrations of RAD001 ( $C_{\min}$ ) and concentration at 2 hours post-dose ( $\pm$  30 mins,  $C_{2h}$ ) will be summarized with descriptive statistics and presented graphically over time. Dose proportionality will be explored with a power model using the actual doses to fit log-trough level data. The potential relationships between  $C_{\min}$  and efficacy/safety endpoints and between  $C_{2h}$  and efficacy/safety endpoints will be explored. A logistic regression model will be used for angiomyolipoma response with  $C_{\min}$  or  $C_{2h}$ , with or without log-transformation, as an independent variable and stratified by the protocol stratification factor. The relationship between RAD001 concentration and safety will be explored by modeling events of CTC grade 3 or above with a generalized estimating equation with  $C_{\min}$  or  $C_{2h}$ , with or without log-transformation, as an independent variable and patients as random effects. Appropriate stratification and/or covariates may be applied in the model.

The measured RAD001 PK levels will be used in future analyses, along with RAD001 PK data from other studies (including, but not restricted to: [CRAD001M2301] (SEGA), [CRAD001C2239] (pancreatic neuroendocrine tumors), [CRAD001C2240] (renal cell carcinoma), [CRAD001C2244] (pediatric medulloblastoma), phase 1 studies [CRAD001C2101], [2102], [2104], [2106], [2107], [2108]). These analyses may use non-compartmental and population PK methods with the goal of comparing the results from this protocol with appropriate reference populations (in other tumor types), and thus to characterize PK in the target population with respect to exposure. The population PK analyses across studies will be reported separately, i.e., not as part of the CSR for study M2302.

#### **10.5.10 Biomarkers**

The effect of RAD001 on biochemical tumor markers and on angiogenesis markers (e.g., VEGF, basic FGF, PLGF, soluble VEGF receptor1 and soluble VEGF receptor2) will be analyzed using summary statistics for raw data and changes from baseline and also using longitudinal models. Relationships between ligands and corresponding soluble receptors will also be examined both relative to baseline and longitudinally.

Mutational analysis of *TSC1* and *TSC2* genes will be correlated with angiomyolipoma response rate and time to angiomyolipoma progression.

### 10.5.11 Evaluation after everolimus discontinuation

Patient who discontinue everolimus for reasons other than angiomyolipoma progression, and who subsequently do not receive systemic treatment with an mTOR inhibitor, will be analysed specifically. Data included in this analysis will be data from the follow-up phase (until the end of the extension phase) and/or from the non-interventional follow-up phase.

Reasons for everolimus discontinuation and for non-inclusion in the non-interventional follow-up phase will be presented for this population. A table of demographic characteristics at start of everolimus and duration of everolimus treatment will be produced in order to appreciate the selection biases.

Sum of volumes of target angiomyolipoma lesions (the ones identified before the start of everolimus) will be described at the time of everolimus discontinuation (end of treatment visit or non-interventional follow-up entry visit) and at the time of the one-year follow-up scan (i.e. scan performed one year after everolimus discontinuation), or an earlier scan which was performed following an angiomyolipoma-related bleeding event ( $\geq$  grade 2), or prior to any intervention such as the start of systemic mTOR treatment, embolization or nephrectomy.

The effect of stopping everolimus on tumor growth will be described in terms of change and percentage change in the sum of the angiomyolipoma target lesions volume from the start of everolimus and from the time of everolimus discontinuation (scan performed at the end of everolimus treatment). Individual plots of sum of volumes of target angiomyolipoma lesions by time will also be performed to illustrate the tumor evolution after stopping everolimus. Similar analyses will be conducted to describe the changes in kidney volume.

The number of patients with at least one new angiomyolipoma lesion  $\geq 1.0$  cm in longest diameter and one angiomyolipoma-related bleeding of grade  $\geq 2$  assessed at the one-year follow-up scan will be tabulated.

If the number of patients included in this analysis is sufficient, the angiomyolipoma progression rate one year after everolimus discontinuation will be provided with exact 95% confidence intervals (Clopper and Pearson 1934). The angiomyolipoma progression will be defined as in Section 7.5.2 of the protocol, i.e. one or more of the following criteria should be observed at the one-year follow-up scan:

- an increase from nadir of 25% or more in angiomyolipoma volume to a value greater than value just prior to everolimus starting date (where angiomyolipoma volume is the sum of the volumes of all target angiomyolipomata identified prior to everolimus start and where nadir is the lowest angiomyolipoma volume achieved by the patient previously in the everolimus period (including the value just prior to everolimus starting date))
- an increase from nadir of 20% or more in the volume of either kidney to a value greater than value just prior to everolimus starting date, where nadir is the lowest kidney volume obtained for the patient, separately for each kidney, previously in the everolimus period (including the value just prior to everolimus starting date)
- the appearance of a new angiomyolipoma  $\geq 1.0$  cm in longest diameter
- angiomyolipoma-related bleeding grade  $\geq 2$  as defined by NCI CTCAE, version 3.0.

In addition, if most patients have small AML lesions (less than 1 cm) at the end of everolimus treatment, the sum of the angiomyolipoma target lesions volume identified at the end of

everolimus treatment with a diameter greater than 1 cm will be described at the time of everolimus discontinuation and at the one-year follow-up scan. The change and percentage change in volume from the time of everolimus discontinuation will also be presented.

If the number of patients included in this analysis is sufficient, the angiomyolipoma progression rate 1-year following everolimus discontinuation will be provided with exact 95% confidence intervals (Clopper and Pearson 1934). The angiomyolipoma progression following everolimus discontinuation will be defined as one or more of the following:

- an increase of 25% or more in angiomyolipoma volume from the end of everolimus treatment (where angiomyolipoma volume is the sum of the volumes of target angiomyolipomata identified as greater than 1 cm at the time of everolimus discontinuation)
- an increase of 20% or more in the volume of either kidney from the end of everolimus treatment
- the appearance of a new angiomyolipoma  $\geq 1.0$  cm in longest diameter
- angiomyolipoma-related bleeding grade  $\geq 2$  as defined by NCI CTCAE, version 3.0.

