## 4.6 Non-interventional follow-up phase

For patients who permanently discontinue everolimus (off-study) at the completion of the extension phase for reasons other than angiomyolipoma progression, a single CT/MRI scan of the kidney will be collected one-year after the last study treatment date. If angiomyolipoma bleeding ( $\leq$  grade 2) occurs, or if intervention is needed at any time during this one-year non-interventional period, a CT/MRI will be completed prior to starting any intervention and the patient will discontinue this non-interventional follow-up phase. Interventions include treatment with systemic mTOR inhibitors such as everolimus or rapamycin, embolization, or (partial) nephrectomy. These additional CT/MRIs will be sent for central review. Any use of non-study systemic anti-angiomyolipoma therapies will be recorded during this supplementary one-year period.

Patients who do not have angiomyolipoma progression at the time treatment discontinuation from the extension phase and are being followed with CT/MRI tumor assessments will exit the study, unless the patient qualifies and elects to participate in the non-interventional follow-up phase. Patients who previously discontinued treatment with everolimus during the extension phase and have not yet taken their first annual CT/MRI may also be included in this non-interventional follow-up phase, if otherwise eligible.

Patients must report to the site any angiomyolipoma-related bleeding events. Diagnostic procedure(s) pertaining to angiomyolipoma-related bleeding should also be reported. All other adverse events that may occur within the one-year period will be collected, as reported by the patient for the DS&E database.

Concomitant medications and non-drug therapies given in treatment of angiomyolipoma or angiomyolipoma-related disease progression must be reported. All other concomitant medications and non-drug therapies will only be collected, as reported by the patient for the DS&E database.

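### Section 10.5.11 contradicts itself on patients who restart an mTOR inhibitor after stopping everolimus, and defines the discontinuation volume in two ways

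*Protocol*

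**What the plan says.** **Population (Section 10.5.11).** The analysis takes patients who stop everolimus for reasons other than progression and "who subsequently do not receive systemic treatment with an mTOR inhibitor, will be analysed specifically". Data come from the follow-up phase, the non-interventional follow-up phase, or both.

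**Which scan is the follow-up scan (Section 10.5.11).** The volume is described at the one-year scan, or at an earlier scan after a bleed of grade 2 or worse, or at one taken "prior to any intervention such as the start of systemic mTOR treatment, embolization or nephrectomy". Section 4.6 and Table 7-3 (footnote b) require that pre-intervention scan in the non-interventional phase, and the patient then leaves the phase.

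**Progression (Section 10.5.11).** The first definition adapts Section 7.5.2 and asks that at least one criterion be seen at the one-year scan. The second measures growth from stopping: "an increase of 25% or more in angiomyolipoma volume from the end of everolimus treatment".

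**Reference scan (Section 10.5.11).** The volume is described "at the time of everolimus discontinuation (end of treatment visit or non-interventional follow-up entry visit"). Change and percentage change are instead taken "from the time of everolimus discontinuation (scan performed at the end of everolimus treatment").

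**Who may enter late (Section 4.6).** "Patients who previously discontinued treatment with everolimus during the extension phase and have not yet taken their first annual CT/MRI may also be included", if otherwise eligible.

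**The concern.** Section 6.7.8 says that the non-interventional phase is there to characterise angiomyolipoma for up to a year after everolimus is permanently stopped. Membership of the analysis population should therefore be settled on the day of stopping. The population sentence settles it later, by whether the patient went back on an mTOR inhibitor. Section 1.4.7 reports that lesions tended to grow again once sirolimus was stopped, so regrowth is a plausible reason to restart. If so, dropping restarters removes patients with more regrowth than average.

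The section also plans to use a scan that only restarters can provide. An analyst must break one of the two rules, and could choose which after seeing the data. The same applies to the discontinuation volume, for which two sources are named with no order of preference and no maximum gap from the last dose.

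**Working it through.** **1. The two rules side by side.** Population sentence: no later systemic mTOR inhibitor. Scan rule: the scan before the start of systemic mTOR treatment is usable. A patient with such a scan has, by definition, started treatment and is outside the population. Both rules cannot be followed.

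**2. The exit scan and the progression rate.** A patient who restarts leaves with an earlier scan and has no off-drug scan at one year. Under the first progression definition, criteria met at that exit scan are not counted. A purely hypothetical example: 20 patients stop, 8 meet progression criteria off drug, and 5 of those 8 restart.
- All stoppers kept, exit scans counted: 8/20 = 40%.
- Restarters excluded: (8 − 5)/(20 − 5) = 3/15 = 20%.
- Restarters kept as non-progressors because exit scans are not counted: 3/20 = 15%.
- Five restart but only 2 of them had progressed, the same 40% as overall: (8 − 2)/(20 − 5) = 6/15 = 40%, so exclusion causes no bias.

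Keeping restarters is therefore not enough; their exit scan must also count.

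**3. Illustration for mean regrowth.** The protocol states no expected regrowth for this analysis, so there is no figure to reproduce. The only related data are the sirolimus means in Section 1.4.7: 53.2% of baseline at 12 months (end of drug) and 85.9% at 24 months. Regrowth is 85.9 − 53.2 = 32.7 points, or 85.9/53.2 − 1 = 61.5% as a ratio of means.

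Assumptions not in the protocol: normally distributed regrowth, SD 15 to 25 points, share restarting *f* from 10% to 40%, and correlation *ρ* between regrowth and the tendency to restart. Mean regrowth among those kept is

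32.7 − ρ × SD × φ(z)/(1 − f), where z is the (1 − f) normal quantile.

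For f = 10%, φ(z)/(1 − f) = 0.1755/0.9 = 0.195. For f = 40%, it is 0.3863/0.6 = 0.644.

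| ρ | Smallest change (f = 10%, SD 15) | Largest change (f = 40%, SD 25) |
|---|---|---|
| 0 | 32.7 | 32.7 |
| 0.3 | 32.7 − 0.3 × 15 × 0.195 = 31.8 | 32.7 − 0.3 × 25 × 0.644 = 27.9 |
| 1 | 32.7 − 15 × 0.195 = 29.8 | 32.7 − 25 × 0.644 = 16.6 |

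With ρ = −0.3 the error reverses, to between 33.6 and 37.5.

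**4. The two discontinuation volumes.** Under Table 7-3 (footnote a) the entry scan is tied to the start of the phase, unless one was done in the past 2 months, and not to the last dose. For a patient who stopped earlier in the extension phase, it could fall anywhere up to just under about 12 months after stopping. On the sirolimus means, an entry scan 6 months after stopping would describe the discontinuation volume as 53.2 + 32.7 × 6/12 = 69.6% of baseline (linear growth) or 53.2 × (85.9/53.2)^0.5 = 67.6% (exponential), against 53.2% at the end of treatment. A patient who stops at the end of the extension phase would be scanned close to the last dose, and the two sources would nearly agree.

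**The case against.** The strongest reply is that the population sentence should be read with the entry rules. Sections 5.1.1 and 6.7.8 speak of patients who do not plan further systemic treatment, and the required pre-intervention scan shows that restarters were meant to contribute. That may well be the intention, but the analysis text says otherwise: it refers to treatment not received, not to treatment not planned. This supports calling the section contradictory rather than a clear exclusion.

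The section also acknowledges selection biases. However, the table it plans covers demographics and duration of treatment for the selected population, and does not show regrowth in those left out.

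It is also fair that the analysis is descriptive, has no hypothesis test, is not listed among the objectives in Sections 3.1 and 3.2, and gives progression rates only if numbers suffice. That limits the weight of the point but does not remove the contradiction.

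Two stronger readings are tempting, and the document does not support them.

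- **A late entry scan biases the one-year progression rate.** It does not. The one-year scan is timed from the last dose. The first progression definition uses the nadir in the everolimus period and the pre-everolimus value; the second uses the end of treatment. Change and percentage change also use the end-of-treatment scan. A late entry scan clearly affects only the described discontinuation volume, and would reach the change analysis only if someone substituted it.
- **The first progression rule is wrong because volume must exceed the pre-everolimus value.** That rule is the protocol's own Section 7.5.2 definition, carried over deliberately. Regrowth below that value still shows in the percentage change from end of treatment and in the individual plots, both planned without condition. Whether the second progression rate is reported only "if most patients have small AML lesions (less than 1 cm) at the end of" everolimus treatment is unclear: the condition is attached to a volume description, and the rate's own paragraph states a different one, sufficient numbers.

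**Conclusion.** The contradiction on restarters is real and stands on the text alone. If the population sentence is followed and regrowth prompts restarting, regrowth and the one-year progression rate may be understated. A reader might infer that they certainly are; the protocol does not show this. The share who restart, the link with regrowth and the spread of regrowth are all unstated. Under the assumed ranges, mean regrowth of 32.7 points would read as 31.8 to 16.6 for correlations from 0.3 to 1, as 32.7 at zero, and higher than 32.7 if the link is negative. The base figure comes from group means for a different drug, with 20 and 18 patients completing the two evaluations, so it shows direction and scale only.

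The double definition of the discontinuation volume is a smaller point, confined to patients who stopped before the end of the extension phase. The primary endpoint is not affected. The correction is worth making because it is cheap and removes choices that would otherwise be made with the data in view.

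**What to change.** Reword Section 10.5.11 as follows.

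- Define the population at discontinuation: all patients who stop everolimus for reasons other than angiomyolipoma progression.
- Include those who later restart an mTOR inhibitor, using their last scan before the restart, and count progression criteria met at that exit scan as well as at the one-year scan.
- Report how many restarters have no off-drug scan. The follow-up phase (Sections 4.4 and 6.7.4) has annual scans that end when non-study systemic therapy starts, and requires no scan before an intervention, so some will have none.
- Use one reference for the discontinuation volume: the end-of-treatment scan or, where none was due, the last on-treatment scan. This matches the change analysis. A scan first taken at entry after a drug-free interval should not serve as that reference.

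The cost is a text change with no new assessments. The reported off-drug progression rate may be higher, and some restarters will contribute shorter follow-up or no off-drug scan at all.
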